## **5 Participant discontinuation/withdrawal**

### **5.1 Participant discontinuation/Withdrawal from the study**

A participant may be withdrawn at any time, at the discretion of the investigator, for safety, behavioural, compliance, or administrative reasons.

If the participant withdraws consent for disclosure of future information, FIND may retain and continue to use any data collected before the withdrawal of consent.

If a participant withdraws from the study, he/she may request destruction of any samples taken and not tested, and the investigator must document this in the site study records. Participants who withdraw from the study will still have access to standard medical care.

### **5.2 Loss to follow up**

No follow up visits are planned for study participants and as such there will be no incidents of loss to follow up.

## **6 Study procedures**

Study procedures and their timing are summarized in the schedule of assessments (see Table 1) and outlined in Figure 2 below. Protocol waivers or exemptions are not allowed and adherence to the study design requirements, including those specified in the schedule of assessments, is essential and required for study conduct.

All screening evaluations must be completed and reviewed to confirm that participants meet all eligibility criteria. The investigator will maintain a screening log to record details of all participants screened and to confirm eligibility or record reasons for screening failure, as applicable.

A study laboratory manual will be compiled with all necessary details for on-site implementation and running of the study.

**Figure 2:** Details of the study procedures, sample flow and timing of testing

[figure not shown]

## 6.1 Participant enrolment

Enrolment will be done at primary healthcare facilities by trained staff.

All individuals attending the healthcare facilities for any health-related issue will be invited to participate in the study.

Individuals will be screened for eligibility and must provide their written consent to participate. After obtaining the signed consent, a participant ID is assigned to him/her and the participant is recorded in the enrolment log.

A participant who is not yet registered at the local healthcare facility, will be entered into care through the locally required registration procedure.

At enrolment, the following information will be collected for each participant, based on verbal information provided by the individual:

- Age
- Gender
- HCV status (known/unknown)
- Medications taken (including antiretrovirals)
- Recent vaccination (within the last 12 months)
- Concomitant infections (including HIV and approximate date of last negative HIV test, if applicable)

After recording the participant's demographic and clinical data in the dedicated Participant Worksheet, blood samples can be collected to perform all necessary study testing.

## 6.2 RDT testing

### 6.2.1 Fingerstick blood

Fingerstick blood will be collected according to each manufacturer's IFU, e.g. with a provided pipette or capillary. All RDTs for a single participant will be performed by the same operator, who is a trained healthcare worker at the facility. The three selected study RDTs have an incubation time of 10-20 min prior to result readiness, which will allow for all RDTs to be started consecutively and read more or less simultaneously, once the incubation time is over and within the allowed reading time frame (see Table 3).

Results of the study RDTs will be read before results of the WHO PQed RDT and all results will be recorded by the operator into the Participant Worksheet.

Any invalid RDT runs will be repeated immediately, using a fresh drop of fingerstick blood, EDTA plasma or serum.

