## Schedule of assessment

**Table 1:** Schedule of assessment

|                                                       | Daily activities per participant in primary healthcare sites |                                                                                  | Weekly activities in reference laboratories |                                                              |
|-------------------------------------------------------|--------------------------------------------------------------|----------------------------------------------------------------------------------|---------------------------------------------|--------------------------------------------------------------|
| Recruitment                                    | Day 1                                                        | Assessment of eligibility                                                        |                                             |                                                              |
|                                                       | Day 1                                                        | Obtaining informed consent                                                       |                                             |                                                              |
|                                                       | Day 1                                                        | Collection of demographic information                                            |                                             |                                                              |
| Testing procedures with participant present    | Day 1                                                        | Fingerstick whole blood testing on three study HCV RDTs and one WHO PQed RDT     |                                             |                                                              |
|                                                       | Day 1                                                        | Fingerstick whole blood testing on HIV RDT                                       |                                             |                                                              |

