|                                                       | Day 1                                                        | Collection of venepuncture blood in EDTA plasma and serum tubes                  |                                             |                                                              |
| Testing procedures without participant present | Day 1                                                        | Centrifugation and separation of EDTA plasma and serum                           | Days 2-7                                    | HCV and HIV RNA confirmatory testing of RDT-positive samples |
|                                                       | Day 1                                                        | Preparation of EDTA plasma and serum aliquots                                    | Days 2-7                                    | EDTA plasma EIA/LIA reference testing                        |
|                                                       | Day 1                                                        | EDTA plasma and serum testing on three study HCV RDTs and one WHO-PQ RDT         |                                             |                                                              |
| Data entry                                     | Day 1-7                                                      | Transcription of Participant Worksheet information and results into Open Clinica |                                             |                                                              |

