#### **4.3.2 Potential bias**

Participants will be enrolled sequentially as they present to the healthcare facility. Eligibility screening and consenting will be done by a person other than the healthcare professional who performs the test to avoid bias in RDT reading in case of a known HCV status. Patients with known HCV serology status will be instructed not to share this status with the HCV RDT tester.

Once the set enrolment targets for HCV negative individuals is reached, only individuals with known HCV-positive status will continue be enrolled in the study to meet required enrolment targets for HCV positive individuals. There is a risk to introduce bias in RDT interpretation, if all enrolled patients are known to be HCV positive. To minimise this risk, known HCV positive patients will be contacted and invited to participate in the study from the beginning of recruitment, to present to the facilities in the same timeframe as individuals of unknown, and thus often negative, HCV status.

The SD Bioline HCV RDT (WHO PQed) will be performed after the performance of the index tests to avoid interpretation bias by the reader based on the results of the WHO PQ-approved test.

EDTA plasma and serum samples will be tested freshly on all RDTs on the same day of sample collection to avoid difference in sample age compared to fingerstick whole blood from the same participant and between samples from different participants.

All reference tests will also be performed on fresh EDTA plasma samples within the allowed sample stability timeframe at 4°C (as per manufacturer's IFU).

The laboratory technicians who perform reference testing, will not have access to the RDT results at the time of testing, as they will not require access to Open Clinica, where RDT results are

entered. This will minimize bias in LIA result interpretation, which is based on visual line intensity scoring. There is no bias in EIA result interpretation, as it is based on electronic read-outs (see section 10.2 Data management).

There is a risk of bias in LIA interpretation due to visual interpretation. This will be addressed by the scoring of all blots by two independent readers and joint discussion in case of discrepant interpretations. In case the two readers cannot agree, a third reader will be asked to score the results independently.

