## 6.3 Venous blood draw and aliquot preparation

Once the fingerstick whole blood collection procedure is completed, the participant will proceed for a venous blood draw of 2 x 5 ml whole blood in an EDTA plasma tube and 1x 3 ml whole blood in a serum tube. All tubes will be pre-labelled with a study specific ID.

After the appropriate clotting time for the serum, all tubes will be centrifuged at a time and speed indicated by the tube manufacturer.

Plasma samples will subsequently be aliquoted in 3x 1 ml aliquots (for HCV RNA PCR, genotyping and potential repeat testing) and 4x 0.5 ml aliquots for RDT and reference testing. Serum samples will be aliquoted in 3x 0.5 ml aliquots for RDT testing.

After aliquot preparation, RDT testing on the EDTA plasma and serum samples will be performed. All other samples will be stored at 4°C until cooled transportation to the reference laboratory. Samples can be stored at 4°C for up to 7 days until EIA and LIA testing, according to the sample stability provided in the manufacturer's IFU [21-23].

All left-over samples will be stored at the reference laboratories at -70°C until the study is completed. Once the study is completed, the samples will be transferred to the FIND sample repository at ZeptoMetrix (for storage time and intended use of left-over samples, see section 6.5).

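### The SD Bioline-last rule protects reading within a specimen type but not across them: nothing in the protocol text masks plasma and serum readings to the same participant's fingerstick results

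*Protocol*

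**What the plan says.** Four parts of the protocol bear on this.

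- **Order of tests, and why.** Section 4.3.2: "The SD Bioline HCV RDT (WHO PQed) will be performed after the performance of the index tests to avoid interpretation bias by the reader". Section 6.2.1 adds the reading order: "Results of the study RDTs will be read before results of the WHO PQed RDT".
- **Operator.** Section 6.2.1: "All RDTs for a single participant will be performed by the same operator, who is a trained healthcare worker at the facility". The operator enters the results in the Participant Worksheet.
- **First round.** Table 1 (Schedule of assessment), Day 1, participant present: "Fingerstick whole blood testing on three study HCV RDTs and one WHO PQed RDT".
- **Second round.** Table 1, Day 1, participant no longer present: "EDTA plasma and serum testing on three study HCV RDTs and one WHO-PQ RDT". Section 6.3 places this after the venous draw, clotting, spinning and splitting into aliquots: "After aliquot preparation, RDT testing on the EDTA plasma and serum samples will be performed". Section 4.3.2 keeps it on the day of collection: "EDTA plasma and serum samples will be tested freshly on all RDTs on the same day of sample collection".

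Section 4.3.2 describes two forms of masking. RDT operators are kept from HCV status known before enrolment, and reference-laboratory technicians have no access to RDT results. Section 4.3.1 explains the coded labels only as a guard against sample mix-up.

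**The concern.** RDTs are read by eye, and a faint line is a judgement. The protocol accepts that knowing another test's result can bias that judgement. It orders SD Bioline last for this reason, and it gives the visually scored LIA two independent readers and masking to RDT results.

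The plasma and serum index readings have no comparable protection from what was seen an hour or so earlier, or whenever the fingerstick strips were read. The reader may know SD Bioline's verdict on that person and each study RDT's own fingerstick verdict. This does not depend on prior HCV history, so it also affects participants of unknown status.

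At stake are the plasma and serum estimates for primary outcome 1.1 and the agreement with SD Bioline for secondary outcome 2.1. Section 1.1 intends these data for WHO prequalification and CE-marking. Section 6.6.3 bases performance on initial results only, so later repeats cannot correct a reading that was swayed.

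**Working it through.** No stated figure is in dispute. The check follows one participant through the plan, counts the exposed estimates, and then asks whether a direction of bias can be claimed.

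**1. Sequence.** Table 3 gives total test times of 15, 20 and 25 minutes for the three study RDTs. Plasma and serum strips cannot start until the tubes have been drawn, clotted, spun and aliquoted, and they then need 10 to 20 minutes of incubation. Table 1 also lists the whole fingerstick round before this step. That the fingerstick strips are read first is therefore an inference, but a strong one. The protocol gives neither a clotting time nor a test time for SD Bioline.

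**2. Operator.** The same-operator sentence stands under a fingerstick heading but speaks of all RDTs for a participant. The closing sentence of the same section plainly covers the other specimens: "Any invalid RDT runs will be repeated immediately, using a fresh drop of fingerstick blood, EDTA plasma or serum". The protocol has no other operator rule for plasma or serum.

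**3. What the ordering rule covers.** Section 4.3.2 does not limit the rule to one specimen. Within each round the study strips can be read before that round's SD Bioline strip. Across rounds the order is:

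| Reading | Same participant's results already known to a single operator |
|---|---|
| Fingerstick study RDTs | No SD Bioline result |
| Fingerstick SD Bioline | Fingerstick study RDTs |
| First venous specimen, study RDTs | All four fingerstick results, SD Bioline included |
| Second venous specimen, study RDTs | All four fingerstick results and those of the first venous specimen |

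**4. Exposure.** 3 study RDTs × 3 specimen types = 9 sets of estimates. 3 study RDTs × 2 venous specimens = 6 exposed sets, for outcome 1.1 and again for outcome 2.1.

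**5. Can a direction be claimed for outcome 1.1?** Let s be true plasma sensitivity, k the share of antibody-positive participants already read positive on fingerstick, and f the share of conflicting readings that give way to the earlier result. Take s = 0.95 (the planning value in 8.2). No document gives f, so every value of f is an assumption.

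- *Only missed plasma strips are changed to positive* (misses assumed independent of the fingerstick result): apparent sensitivity = s + (1 − s)·k·f.
  - f = 0.10, k = 0.90: 0.95 + 0.05 × 0.90 × 0.10 = 0.9545
  - f = 0.50, k = 0.90: 0.95 + 0.05 × 0.90 × 0.50 = 0.9725
  - f = 0.50, k = 1.00: 0.95 + 0.05 × 1.00 × 0.50 = 0.975
- *Readings give way in both directions*: apparent sensitivity = s + f·(k − s).
  - f = 0.10, k = 0.90: 0.95 + 0.10 × (−0.05) = 0.945
  - f = 0.50, k = 0.90: 0.95 + 0.50 × (−0.05) = 0.925

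For scale, the Wilson 95% interval around 0.95 with n = 440 runs from 0.9255 to 0.9668. The first assumption raises the estimate and the second lowers it, and the documents do not say which applies. Neither size nor sign can be stated.

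**6. Outcome 2.1.** Here the direction is clearer. For plasma and serum, both the study strip and the SD Bioline strip are read by someone who knows SD Bioline's fingerstick result. If that knowledge acts at all, it pulls both readings towards one answer, which raises agreement and kappa.

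**The case against.** The strongest reply is that the same-operator sentence belongs to the fingerstick procedure. Section 4.3.1 speaks of one operator running four RDTs in sequence, which fits one specimen type rather than all twelve strips. On that reading the protocol has no operator rule for plasma and serum. The layout of the Participant Worksheet is not described, and Figure 2 or the study manual could settle operator, batching or record layout.

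This stands in part. The reach of 6.2.1 to plasma and serum is an inference, though the better reading of the text. But the narrow reading does not supply masking. It leaves open who reads the later strips and what they may see, and section 4.3.2, where such a safeguard belongs, is silent.

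Two other replies also stand. The operators are trained on bands of different intensity, which should reduce misreading of faint lines. And large mixed-order batches would carry their own risk. At 15 to 25 participants a day per site, plasma and serum mean 4 RDTs × 2 specimens = 8 strips each, so 120 to 200 strips a day, and Wantai results are stable for only 5 minutes.

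A reader might infer that the ordering rule works for fingerstick blood alone. It does not say so, and it still operates within the plasma round and within the serum round.

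**Conclusion.** The gap is real and should be closed before enrolment, because it cannot be repaired in analysis. As written, the protocol leaves plasma and serum readings open to knowledge of the same participant's earlier results, SD Bioline included. Six of nine sets of primary estimates are exposed. That is a count of exposure, not of effect: size and direction for outcome 1.1 are unknown. For outcome 2.1 in plasma and serum, inflated agreement is the likely direction, of unknown size.

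This rests on two inferences: that 6.2.1 extends to all specimen types, and that fingerstick strips are read before the venous ones. It also assumes that Figure 2 and the study manual add no masking step.

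Two stronger conclusions are not supported. First, one might take the 90% (whole blood) and 95% (plasma and serum) planning values as a 5-point specimen difference and compute how far it would shrink. Sections 2 and 8.4 plan no contrast between specimen types, section 3.2 compares each with the reference standards, and the planning values are conservative assumptions for sample size. Second, the composite reference is not compromised: EIA and LIA staff do not see RDT results.

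**What to change.** - In 6.2.1, limit the same-operator rule to the four RDTs on one specimen type.
- Record plasma and serum results on a separate sheet that shows no fingerstick results and identifies the sample only by the pre-printed aliquot label already provided for in 4.3.1.
- Where more than one trained operator is already on duty, give a participant's plasma and serum strips to one who did not read that participant's fingerstick strips.
- In 4.3.2, state that RDT results from another specimen of the same participant are not available at reading.
- Testing in mixed order across participants is optional, and only in small runs that keep to each RDT's reading window.
- Where a site has only one operator, report the remaining lack of masking as a limitation of the plasma and serum estimates.

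The cost is one more result sheet, slightly more transcription, and linkage by label. No extra staff, samples or tests are needed, and same-day testing is kept. If Figure 2 or the study manual already contains such a step, it is enough to state it in 4.3.2 and align 6.2.1.

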## 6.3 Venous blood draw and aliquot preparation

Once the fingerstick whole blood collection procedure is completed, the participant will proceed for a venous blood draw of 2 x 5 ml whole blood in an EDTA plasma tube and 1x 3 ml whole blood in a serum tube. All tubes will be pre-labelled with a study specific ID.

After the appropriate clotting time for the serum, all tubes will be centrifuged at a time and speed indicated by the tube manufacturer.

Plasma samples will subsequently be aliquoted in 3x 1 ml aliquots (for HCV RNA PCR, genotyping and potential repeat testing) and 4x 0.5 ml aliquots for RDT and reference testing. Serum samples will be aliquoted in 3x 0.5 ml aliquots for RDT testing.

After aliquot preparation, RDT testing on the EDTA plasma and serum samples will be performed. All other samples will be stored at 4°C until cooled transportation to the reference laboratory. Samples can be stored at 4°C for up to 7 days until EIA and LIA testing, according to the sample stability provided in the manufacturer's IFU [21-23].

All left-over samples will be stored at the reference laboratories at -70°C until the study is completed. Once the study is completed, the samples will be transferred to the FIND sample repository at ZeptoMetrix (for storage time and intended use of left-over samples, see section 6.5).

#### **6.4 Reference and confirmatory testing**

After transportation to the reference laboratory, all samples will be stored at 4°C until EIA1, EIA2 and LIA reference testing, and HCV and HIV confirmatory testing, as well as HCV genotyping. All procedures will be performed within the allowed sample stability timeframe for 4°C storage by the manufacturer.

EIA1, EIA2 and LIA reference testing on EDTA plasma samples will be performed in batches. Performance of these test is known to be equivalent in serum and EDTA plasma, according to the manufacturers' IFU. Due to this, reference testing will only be performed in EDTA plasma. For each EIA run, the manufacturers' positive and negative controls will be used and results interpreted according to the IFU. Additionally, a plate-internal run control (IRC) of a known HCV-positive sample, will be added to each EIA plate, to monitor EIA consistency. The expected value of this IRC will be set during three independent control runs prior to the start of any EIA reference testing. IRC standard deviations and acceptance limits will be set based on the IRC results from these three control runs. Further details will be provided in the study manual.

#### **6.5 Specimen collection, handling, transport and storage**

All samples will be handled in accordance with standard local biosafety rules and maintained at 4°C for transportation.

The maximum amount of blood collected from each participant over the duration of the study, will not exceed 13 ml of venous blood and 4 drops of fingerstick blood (approximately 50 µl each). Repeated or unscheduled samples may be taken for safety reasons or for technical issues with the samples.

The fingerstick blood samples will be used immediately on the RDTs. The 13 ml venous blood will be collected in 2x 5 ml EDTA tubes and a 1x 3 ml serum tube. Plasma and serum will be separated by centrifugation within a maximum of 4 hours from blood collection at the healthcare facilities. The plasma and serum aliquots will be stored at 4°C until transfer to the reference lab for EIA/LIA, reference and confirmatory testing.

Left-over samples will be archived at the ZeptoMetrix biorepository for a maximum of 5 years or until FIND agrees that samples can be destroyed. For sample destruction (e.g. upon withdrawal of consent to use blood samples), best practices for management of infectious waste should be followed.

